## Abstract

**Background:**

Chronic kidney disease (CKD) is a well-established complication in people with diabetes mellitus. Roughly one quarter of prevalent patients with diabetes exhibit a CKD stage of 3 or higher and the individual course of progression is highly variable. Therefore, there is a clear need to identify patients at high risk for fast progression and the implementation of preventative strategies. Existing prediction models of renal function decline, however, aim to assess the risk by artificially grouped patients prior to model building into risk strata defined by the categorization of the least-squares slope through the longitudinally fluctuating eGFR values, resulting in a loss of predictive precision and accuracy.

**Methods:**

This study protocol describes the development and validation of a prediction model for the longitudinal progression of renal function decline in Caucasian patients with type 2 diabetes mellitus (DM2). For development and internal-external validation, two prospective multicenter observational studies will be used (PROVALID and GCKD). The estimated glomerular filtration rate (eGFR) obtained at baseline and at all planned follow-up visits will be the longitudinal outcome. Demographics, clinical information and laboratory measurements available at a baseline visit will be used as predictors in addition to random country-specific intercepts to account for the clustered data. A multivariable mixed-effects model including the main effects of the clinical variables and their interactions with time will be fitted. In application, this model can be used to obtain personalized predictions of an eGFR trajectory conditional on baseline eGFR values. The final model will then undergo external validation using a third prospective cohort (DIACORE). The final prediction model will be made publicly available through the implementation of an *R shiny* web application.

**Discussion:**

Our proposed state-of-the-art methodology will be developed using multiple multicentre study cohorts of people with DM2 in various CKD stages at baseline, who have received modern therapeutic treatment strategies of diabetic kidney disease in contrast to previous models. Hence, we anticipate that the multivariable prediction model will aid as an additional informative tool to determine the patient-specific progression of renal function and provide a useful guide to early on identify individuals with DM2 at high risk for rapid progression.

## Introduction

Chronic kidney disease (CKD) has become an increasing global health problem, partly due to the continuously rising incidences of diabetes mellitus, obesity, and hypertension [1]. It is estimated that 8 to 16% of the world’s population suffer from CKD, and the rate is even higher in people with DM2, where cross-sectional studies report percentages of roughly 25% [2]. Ninety-five percent of people with early CKD are unaware of their disease [3]. However, early prediction of the continuous decline in kidney function could provide an additional resource for personalized preventative care [4]. Personalized risk assessment based on large study cohorts could therefore offer several potential benefits to the preventive care for people with DM2 such as early detection followed by monitoring to guide treatment and potentially slow the progression of the decline of kidney function as expressed by the estimated glomerular filtration rate (eGFR) [4]. Despite the accumulated knowledge with regard to CKD nowadays, identifying individuals at high risk for fast disease progression has proven to be challenging because longitudinal eGFR slopes not only vary between patients (inter-patient variability), but eGFR measurements also fluctuate within each patient over time (intra-patient variability) [5].

Nevertheless, several prediction models for the progression of renal function decline have previously been developed in various populations. It is of note that the models which were developed in studies from the last decade may no longer be applicable nowadays, because the new treatment classes of SGLT2-blocker and mineralocorticoid receptor antagonists have dramatically changed the course of CKD progression [6–8]. In addition, existing predictive models have mainly considered hard renal endpoints such as incidence or end-stage renal failure [9, 10]. Studies focused on renal function have mainly considered simplifications of the longitudinal eGFR trajectory by dichotomization of the expected eGFR slope. For instance, Subasi et al. [11] conducted a pilot study based on a randomized double-blinded treatment trial, the African American Study of Kidney Disease and Hypertension (AASK), in order to predict the rate of kidney function decline. The least-squares slopes of GFR decline from the 6-month time point until censoring were used to define rapid (i.e., an absolute slope < 3mL/min/1.73m^2^/year) and slow (i.e., absolute slope in between 1 and 3mL/min/1.73m^2^/year) progressors for this study. Similarly, Vigil et al. [12] aimed towards the identification of predictors of a rapid decline of renal function defined as an annual eGFR loss > 4 mL/min/1.73m^2^. However, covariates considered for selection in this analysis were chosen on the basis of their significance in univariable analysis (or by their clinical or biological relevance). Despite its popular use for data reduction, univariable prefiltering has been shown to lead to suboptimal or biased selection results [13]. Pena et al. [14] showed that a panel of novel biomarkers improves the prediction of renal function decline in people with DM2. In contrast to the other mentioned studies, renal function decline was not dichotomized. The eGFR slope was estimated using linear regression and then constituted the outcome of interest in its continuous form. People with an observed eGFR decline larger than −3mL/min/1.73m^2^ were considered stable, all others were considered to be rapid progressors in terms of kidney function decline. Then, a person’s risk was assessed by dichotomizing the observed decline in these two groups and comparing it with the predicted probabilities of eGFR decline. The threshold of −3mL/min/1.73m^2^ was selected based on literature, which however included older studies without the current state-of-the-art therapy of diabetic kidney disease, where a GFR loss of only 1mL/min//1.73m^2^/year is standard [14–17]. Furthermore, molecular data in regular clinical care is usually not easily available and no validated reference values exist for these markers.

In this study, we will apply state-of-the-art methodology to avoid deficiencies of previous attempts in prediction models for renal function decline. We will directly incorporate the repeated eGFR measurements per person as an outcome vector into a multivariable mixed-effects model accounting for the dependence of the repeated measurements of eGFR and the clustered data structure due to the use of two multicenter prospective study cohorts. We will also provide the methodology to condition a prediction on an available baseline value of eGFR, facilitating predictions regardless of whether a baseline eGFR is available or not. In contrast to the commonly applied approaches, the repeated values of eGFR across follow-up visits will not be used for slope estimation followed by categorization to infer groups of the severity of loss in kidney function (e.g., stable, mild, and rapid progression) prior to model development. The proposed approach will enable the identification of groups of patients with a high risk of rapid renal function decline by longitudinal prediction of subject-specific eGFR trajectories, thereby providing the probability of exceeding a prespecified cutpoint of eGFR decline per year. After the planned external validation, our model will be implemented as a web tool and can be clinically applied to identify people with DM2 at increased risk of rapid decline in kidney function, or as a supporting tool for clinicians in medical decision-making so that patients can be prompted to seek medical care before a significant deterioration in kidney function occurs.

### Objective

The main objective of the planned analysis is the development, internal-external, and external validation of a personalized prediction model for eGFR loss per year in Caucasian people with DM2. It is based on clinical information and laboratory measurements recorded at baseline. A secondary aim is the implementation of the externally validated prediction model as a publicly available web application to facilitate general applicability in clinical care based on data from recent eras using modern therapy.

## Research design and methods

### Data source

The study cohort for a model building comprises individuals from two distinct prospective observational studies (PROVALID, GCKD) covering a wide range of CKD states [18, 19]. For the purpose of external validation, a third prospective cohort study (DIACORE) will be used [20].

#### PROVALID - PROspective cohort study in patients with type 2 diabetes mellitus for VALIDation of biomarkers

The PROVALID study cohort consists of around 4000 people with DM2 of whom information on medical history, physical status, laboratory measurements, and medication have been prospectively collected. Patients who are being taken care of at the primary healthcare level in five European countries (Austria, Hungary, Netherlands, Poland, and Scotland) were recruited between 2011 and 2015 and followed for at least 5 years. Participants had to be aged 18–75 years and had an incident or prevalent DM2 defined as treatment with hypoglycaemic drugs or according to ADA guidelines at the time point of study entry. The presence of CKD at study entry was not an exclusion or inclusion criterion. For the full inclusion and exclusion criteria of patients, see Table 1. The aim of the study was to investigate regional differences in the course of diabetic nephropathy to determine the 5-year cumulative incidence of renal and cardiovascular outcomes and to identify predictive biomarkers for the eGFR trajectory in patients with DM2.

**Table 1 Tab1:** Overview of the inclusion and exclusion criteria of PROVALID, GCKD, and DIACORE

Study cohort	Study setting	
	Inclusion	Exclusion
PROVALID	▪ Aged 18–75 years ▪ Incident or prevalent DM2 with/without CKD	• Active malignancy requiring chemotherapy
GCKD	▪ Aged 18–74 years ▪ Caucasian ethnicity ▪ eGFR: 30–60 mL/min/1.73m^2^with or without urinary albumin excretion ▪ eGFR > 60 mL/min/1.73m^2^ - Albumin excretion of > 300mg/g creatinine - Proteinuria > 500mg/day	▪ Active malignancy in the 24 months prior to inclusion ▪ Renal or other transplantations ▪ NYHA IV heart failure
DIACORE	▪ Aged ≥ 18 years ▪ Caucasian ethnicity ▪ Prevalent DM2	▪ On chronic renal replacement therapy ▪ Active malignancy ▪ Pregnancy ▪ Further diseases and infections

#### GCKD—German chronic kidney disease

The prospective cohort study GCKD consists of around 5000 people with CKD. Patients aged 18–74 years and suffering from CKD were included in case of an eGFR between 30 and 60 ml/min/1.73m^2^ with or without urinary albumin excretion (CKD KDIGO Stage 3) or a better preserved eGFR in the presence of urinary albumin excretion >300 or protein excretion >500mg/day, and were followed up to 10 years. For the full inclusion and exclusion criteria of patients, see Table 1. Out of the 5000 recruited individuals, 1800 had diabetes and therefore represent the relevant patient subset for the prediction model in this work. The follow-up visits were set up in bi-yearly intervals. The main objective of the GCKD study cohort was to identify and validate risk factors for CKD, end-stage renal disease (ESRD), and cardiovascular disease (CVD) events.

#### DIACORE—the DIAbetes COhoRtE study

DIACORE is a prospective observational cohort study consisting of 6000 people with prevalent DM2 in Germany with at least 10 years of follow-up. The main objective of this study was the investigation of risk factors associated with the development and progression of diabetic complications through biosampling using high-throughput technologies for the collected biosamples (i.e., transcriptomics, proteomics, and metabolomics). To this end, patient information and blood samples were taken at baseline and at every bi-yearly follow-up visit for at least 10 years after study initiation.

### Target population

The following inclusion criteria will be applied to the individuals from the PROVALID, GCKD, and DIACORE studies for the development and validation of the prediction model in this work:
Caucasian ethnicityPresence of DM2 at baselineeGFR > 30 mL/min/1.73m^2^ at baselineAged 18–75 years at baselineAt least three visits with recorded serum creatinine measurements (including baseline)At least 2 years of follow-up

### Study outcome

The primary outcome of interest for the study is the annual decline in renal function, derived through the use of at least 3 follow-up measurements of eGFR. The eGFR values will be calculated by the equation of the Chronic Kidney Disease Epidemiology Collaboration (CKD-EPI) using the patient’s race, sex, age, and serum creatinine level [21].

### Clinical predictor variables

The candidate variables for consideration in the prediction model were selected by medical experts. Variables of general clinical availability, ease in acquisition, and with clinical acceptance for inclusion in the model will be prioritized. Hence, the following variables will be included in the multivariable outcome model for the decline in renal function (see Table 2): age, sex, body mass index (BMI), smoking status (ever/never smoked), HbA_1c_, urine albumin-to-creatinine ratio (UACR), presence of glucose-lowering medication, presence of lipid-lowering medication, presence of blood pressure-lowering medication, systolic and diastolic blood pressure, hemoglobin, and serum cholesterol. All predictors were measured at baseline, i.e., the first visit after the patient was included in either of the study cohorts. Due to the varying depth of information regarding the medication of an individual in the three cohorts, only drug indication classes will be included as a binary entry (y/n).

**Table 2 Tab2:** Clinical baseline information of study participants within PROVALID, GCKD, and DIACORE

Variable type	Variable	Level of measurement	Unit
Demographics	Age	Continuous	Years
	Sex	Binary	Female-male
Physical status	Smoking	Binary	Never-ever
	BMI	Continuous	kg/m^2^
Laboratory measurements	eGFR	Continuous	mL/min/1.73m^2^
	Systolic blood pressure	Continuous	mmHg
	Diastolic blood pressure	Continuous	mmHg
	HbA_1c_	Continuous	mmol/mol
	Serum cholesterol	Continuous	mg/dl
	Hemoglobin	Continuous	*μ*mol/L
	UACR	Continuous	mg/g
Intake of medication	Blood pressure-lowering	Binary	Yes-no
	Glucose-lowering	Binary	Yes-no
	Lipid-lowering	Binary	Yes-no

### Sample size

Overall, 13 predictors will be included in the prediction model. Guidelines regarding the minimum required sample size for the development of a new multivariable prediction model have been recently proposed by Riley et al. [22]. Using the accompanying R package “pmsampsize” with an assumed average value for eGFR of 78.4mL/min/1.73m^2^ and a standard deviation of 21.4 mL/min/1.73m^2^ [23] in the population, an anticipated *R*^2^ of the model of 0.3 [24] and a shrinkage factor of 0.9, the minimum sample size aimed at minimization of overfit and the precise estimation of the parameters of a prediction model with 13 predictors is 271. Further, since regularization is not taken into consideration in model development due to the abundance of data relative to the number of predictors, the computation with a shrinkage parameter of 0.99 results in a sample size of 3048 required subjects. However, a much larger *R*^2^ is expected, which is why a minimum sample size of 1569 is required for a *R*^2^ of 0.5 and 903 participants for 0.7, respectively. Nevertheless, the development cohort will comprise around 5800 subjects and thus will exceed the minimum required sample size by far.

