More formally, the model for the continuous eGFR values *Y*_*it*_ at time point *t* (*t* = 0, …, *T*) for subject *i* (*i* = 1, …, *n*) is defined by
1$$ {\mathrm{Y}}_{\mathrm{i}\mathrm{t}}={\upbeta}_0+{\mathrm{a}}_{\mathrm{i}}+{\upbeta}_1X+{\upbeta}_2\mathrm{t}+{\upbeta}_3\mathrm{tX}+{\mathrm{b}}_{0\mathrm{i}}+{\mathrm{b}}_{1\mathrm{i}}\mathrm{t}+{\upepsilon}_{\mathrm{i}\mathrm{t}}, $$

with normally distributed residuals $$ {\epsilon}_{it}\sim N\left(0,{\sigma}_{\epsilon}^2\right) $$ with mean 0 and variance $$ {\sigma}_{\epsilon}^2 $$, random country-specific intercepts assumed to be *a*_*i*_~*N*(0, *τ*^2^), the random coefficients (*b*_0*i*_, *b*_1*i*_)~*MN*(0, *G*) (where MN denotes the bivariate normal distribution with an unspecified covariance matrix G, defined by the diagonal elements $$ {\upsigma}_0^2 $$ and $$ {\upsigma}_1^2 $$ and the off-diagonal σ_01_) and the vector of regression coefficients for the clinical independent variables *β* = (*β*_0_, *β*_1_, *β*_2_, *β*_3_). It should be noted that for simplicity of description, we here consider a single clinical predictor variable *X*, where *β*_1_ and *β*_3_ represent the regression coefficients corresponding to the clinical predictor variable and its interaction with time. Without loss of generality, more clinical predictors can be added, each with two regression coefficients for the baseline effects of the predictor and the corresponding interaction with time. When considering restricted cubic splines for a variable, this variable will be represented by several corresponding basis functions in (1).

Model (1) allows to prognosticate baseline and follow-up values of eGFR for a new person *j* given the value of the clinical predictor *X*, assuming that for that new person the random intercept and slope are equal to their expected values of 0. Further, we will assume the expected random country effect of *a*_*j*_ = 0 for the prediction of eGFR in a new individual. In order to incorporate a baseline eGFR measurement *y*_*j*0_ into the prediction, a best linear unbiased predictor (BLUP) of the individual’s random effects can be obtained through the posterior distribution of the random effects. The random intercept for that new subject *j* is then estimated by
2$$ {\hat{\mathrm{b}}}_{0\mathrm{j}}=\frac{\upsigma_0^2\left({\mathrm{y}}_{\mathrm{j}0}-{\hat{\mathrm{y}}}_{\mathrm{j}0}\right)}{\upsigma_0^2+{\upsigma}_{\upvarepsilon}^2}, $$

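### The sample-size calculation counts 13 predictors, but the described model has 27 candidate linear coefficients, so at the anticipated R² of 0.3 about 5800 subjects just miss the 0.99 shrinkage target

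*Protocol article*

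**What the plan says.** The Sample size section of the protocol article states: "Overall, 13 predictors will be included in the prediction model". It applies the pmsampsize criteria with "an assumed average value for eGFR of 78.4mL/min/1.73m^2", "a standard deviation of 21.4 mL/min/1.73m^2" and an anticipated R² "of the model of 0.3 [24] and a shrinkage factor of 0.9", and obtains 271. Because no regularization is planned, it then tightens the target: "the computation with a shrinkage parameter of 0.99 results in a sample size of 3048 required subjects". It goes on to say that the R² should turn out much larger, gives 1569 for 0.5 and 903 for 0.7, and concludes: "the development cohort will comprise around 5800 subjects and thus will exceed the minimum required sample size by far".

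The model itself is set out elsewhere. The Abstract (Methods) describes main effects of the clinical variables together with their interactions with time. Under Prediction model development, equation (1) is written for one predictor and extended as follows: "more clinical predictors can be added, each with two regression coefficients for the baseline effects of the predictor and the corresponding interaction with time". The same section says that time interactions judged clinically relevant are examined and retained if AIC improves, that non-linear variables are given restricted cubic splines, and that regularization is omitted because the sample is large.

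**The concern.** The shrinkage criterion depends on the number of candidate coefficients, not on the number of clinical variables. Entering 13 leaves out the time term and every time interaction.

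Those are the terms that matter most here. The Study outcome section names annual decline in renal function as the outcome, and the predicted slope under Prediction model development is the time coefficient plus the interaction contribution plus the random slope. The 13 coefficients that were counted are the main effects, which describe the level of eGFR. The 14 that were not counted are all the fixed effects in its slope.

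The stated surplus also carries weight in the design: it is the reason given for fitting without regularization and for expecting minimal overfitting. If the required numbers are too low, that reason is weaker than it appears. The comparison figure of 5800 raises a second question, namely whether it is the number that will be analysed.

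**Working it through.** **Inputs.** From Sample size: 13 predictors; R² of 0.3, 0.5 and 0.7; shrinkage S of 0.9 and 0.99; mean 78.4, SD 21.4; development cohort about 5800. From the Abstract and equation (1): two coefficients per predictor plus one for time, so p = 13 + 13 + 1 = 27 without the intercept.

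**Formula.** The governing criterion for a continuous outcome takes the smallest n for which

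S = 1 + (p − 2) / [n · ln(1 − R²app)], with R²app = [R²(n − p − 1) + p] / (n − 1),

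reaches the target. The other criteria are 1 + p(1 − R²)/0.05 for optimism in R², 234 + p for the residual variance, and precision of the intercept. None of them governs in the scenarios below.

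**Reproducing the plan (p = 13).** At R² = 0.3 and n = 3048, R²app = (0.3 × 3034 + 13)/3047 = 0.30299, ln(1 − R²app) = −0.36095, and S = 1 − 11/1100.18 = 0.9900. All four published figures come back exactly.

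**Corrected count (p = 27).** At R² = 0.3 and n = 6934, R²app = (0.3 × 6906 + 27)/6933 = 0.30273, ln(1 − R²app) = −0.36058, and S = 1 − 25/2500.24 = 0.9900.

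| R² | S | Plan (p = 13) | p = 27 | Expected S at n = 5800, p = 27 |
|---|---|---|---|---|
| 0.3 | 0.9 | 271 | 624 | 0.988 |
| 0.3 | 0.99 | 3048 | 6934 | 0.988 |
| 0.5 | 0.99 | 1569 | 3568 | 0.994 |
| 0.7 | 0.99 | 903 | 2054 | 0.996 |

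**Position of 5800.**
- At R² = 0.3 and S = 0.99 the shortfall is 6934 − 5800 = 1134, or 16% of 6934.
- The expected shrinkage there is 1 − 25/2095.78 = 0.988, against the target of 0.99.
- With p = 27 the requirement is 5845 at R² = 0.345 and 5741 at R² = 0.35, so 5800 suffices from about 0.35 upward.
- At R² = 0.3, 22 parameters need 5546 and 23 need 5824, so 5800 supports at most 22.
- One coefficient beyond 27, such as a single spline term, raises the R² = 0.3 requirement to 7211, an increase of 277. The article does not fix the number of spline terms.

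**Where 5800 comes from.** PROVALID has around 4000 participants, and of the GCKD participants "1800 had diabetes and therefore represent the relevant patient subset". The sum 4000 + 1800 = 5800 matches the stated figure. The Target population section then asks for DM2, Caucasian ethnicity, baseline eGFR above 30, age 18–75, at least three creatinine visits and at least two years of follow-up, and the Statistical analysis section restricts the analysis to complete cases. The article does not say how many subjects these steps remove.

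**The case against.** Four points can be made in the plan's favour.

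- **The interactions are conditional.** They enter only if clinically relevant and supported by AIC, so a reader who infers that the fitted model must have at least 27 coefficients goes further than the text. This stands: 27 is a count of candidates. It does not rescue 13, because the criterion concerns the terms considered, and choosing among them by AIC on the same data is itself a source of overfitting.
- **A larger R² is expected.** At 0.5 and 0.7 the corrected minima of 3568 and 2054 lie well below 5800. This also stands. However, 0.3 is the value the plan calls anticipated and the only one for which it cites a source; no basis is given for the larger values.
- **The shortfall is small in effect.** An expected shrinkage of 0.988 against 0.99 is negligible in practice, and the 0.9 criterion needs only 624. This stands, and it limits the point to the stated figures and margin.
- **The formula assumes one observation per subject.** The model uses at least three eGFR values per person, so neither 3048 nor 6934 carries over exactly to a mixed model. This stands, and it applies equally to the plan's own figures.

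On the 5800, some criteria remove few or nobody: PROVALID enrolled only people with DM2, and GCKD already required Caucasian ethnicity and, through its entry criteria, an eGFR of at least 30. The visit, follow-up and completeness requirements apply to both cohorts. The plan expects little missing data.

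**Conclusion.** The point holds as a wrong input count, not as an error of arithmetic. The four stated minima are correct for 13 parameters and too low for the 27 candidate linear terms that the article describes. The claim that 5800 exceeds the minimum by a wide margin fails at the plan's anticipated R² of 0.3 with the 0.99 target. It is supported at R² of 0.5 and 0.7, and 5800 is sufficient from about 0.35.

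A reader might infer that the development cohort is too small or that omitting regularization is unsafe. The documents do not support that: expected shrinkage at 5800 is 0.988 even at R² 0.3. Nor can one conclude that exclusions take the analysed number below any particular minimum, because the article gives no loss rates; what can be said is that 5800 looks like a figure before exclusions.

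The conclusion assumes all 13 time interactions are candidates, no spline terms, n = 5800, and a formula that is only approximate for repeated measurements.

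**What to change.** In the Sample size section:

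- Recompute with the number of candidate parameters, 27 plus any planned spline terms.
- Report 624, 6934, 3568 and 2054 together as the figures for 27.
- State that the formula assumes one observation per subject and is only approximate for the mixed model.
- Label 5800 as the number before the eligibility criteria and the complete-case restriction.
- Replace the claim of a wide margin with the statement that, at n = 5800 and 27 parameters, the 0.99 target is met only if R² is about 0.35 or more.

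No further recruitment is needed and shrinkage of the coefficients need not be made mandatory. The cost is a few sentences and a less favourable stated margin.
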